**Fig 1 pone.0301357.g001:**
[figure not shown]
Flow chart depicting the sequence of project implementation plan.

### Project implementation plan

**Socio-demographic data sheet:**
Socio-demographic data sheet for mothers visiting the immunization clinic will be developed. This will include the respondents’ identification data, viz., age, education, and place of residence, marital status, family type (joint, nuclear, extended) and child birth details.**Postpartum Depression Literacy Scale (PoDLiS)**
The PoDLiS will be used to assess the effectiveness of the video intervention on PPD. PoDLiS is a standardised and validated tool developed by Mirsalimi et al. in 2000 with a Cronbach alpha coefficient of 0.78 [33]. The formal permission has been obtained from the authors for utilising the PoDLiS for this study. It is a 31-item scale that uses 27 variables to measure literacy on the following 7 constructs: the ability to identify postpartum depression, knowledge of risk factors and causes, knowledge and belief of self-care activities, knowledge about professional help available, beliefs about professional help available, attitudes that foster recognition of postpartum depression and appropriate help-seeking, and knowledge of how to look up information related to postpartum depression. Each item is scored on a Likert scale of 1 to 5, with 1 denoting strongly disagree and 5 strongly agree, is used to grade each item. Reverse scoring items receive the opposite score.
The PoDLiS has been used by Poreddi et al. in India to estimate the PPD literacy among postpartum mothers [6]. The tool has not been validated so far for use in India. As a part of the current study the PoDLiS will be translated to Kannada (Vernacular language) and the validity and reliability testing of the same will be undertaken before using the tool for data collection.**Patient Health Questionnaire 9 (PHQ 9)**
The study focuses on postpartum mothers within six months of child birth and who are at risk for PPD. The PHQ 9 tool will be administered to screen the mothers for depression in the study. The PHQ 9 was developed and validated by Kroenke K et al. the internal consistency Cronbach’s alpha coefficient of the tool is 0.86. The mothers will be screened using PHQ 9 in the beginning of the trial and also after 4 to 8 weeks during the post test, as there is a risk that some of them may have later developed the symptoms. This depression assessment instrument is self-administered. It combines other prominent major depressive symptoms with DSM-IV depression criteria in a quick self-report tool that is frequently used for screening and diagnosis [34]. There are nine short statements that make up the scale. A mother selects one of the four options that best describes her feelings during the previous two weeks. Mothers who score 5 or more of the nine depressive symptoms (score >15) are diagnosed with major depression, which requires medical intervention.**Feedback Form**
After watching the video, the mothers will receive a feedback form to rate the videos’ overall presentation and usefulness including the content, story line, language, audio and video quality, message etc. using a 5 point Likert scale.

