### Data collection

The Postpartum Depression literacy scale will be used to conduct the pre and post-test among the postpartum mothers to examine the effectiveness of the video intervention in terms of improving awareness and reducing the stigma. The literacy scale is a self-report measure which will be easy to administer, however in case of mothers who are illiterate, the scale will be administered by the research scholar. The postpartum mothers visiting the Immunization Clinic will undertake the pre-test, screened for PPD and later will be made to watch the video. After watching the video, a feedback form will be provided to the mothers regarding the effectiveness of the video. The post-test will be conducted at an interval of 4–8 weeks of time after pre-test [35] to ensure knowledge retention and also the compliance for posttest, as the mothers will be visiting immunization clinics at 6, 10 and 14 weeks for vaccination of the child as part of the Universal Immunization Program [36]. Lastly the mothers will be re-screened for PPD using PHQ 9. In case a mother scores high on PHQ 9, indicating depression them they will be seen by the trained medical officer (As a part of District Mental Health Program (DMHP), all the PHCs runs ‘Manochaitanya Clinic’ on Tuesdays.) and later mothers will be referred to manochiatanya clinic for further evaluation and treatment by mental health professionals.

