### Study outcome

#### Primary outcome

This video intervention is intended to improve the awareness and reduce stigma on postpartum depression among mothers attending immunization clinics. The same will be assessed using the PoDLiS scale before and after the intervention.The developed educational video will be useful to help identify mothers with PPD which can then lead to early initiation of treatment and improved health outcomes for both mothers and their children. This will be done using the PHQ 9 before and 4–8 weeks after intervention.

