### Statistical analysis

The salient findings from literature search will be summarized and findings will be included for the script. The outcomes of FGDs will be qualitatively analysed. Inductive and thematic theme identification will be done using a descriptive approach. The analysis will be done manually and the themes will be generated based on the codes from the discussion. The findings will be utilized for finalising the video script. The effectiveness of the video intervention will be quantitatively analysed using paired t test. The results will be presented as mean, SD at each time point and 95% CI of the difference between pre and post means. Repeated measures of ANOVA will be used to analyse the change in Postpartum Depression Literacy Scale scores with respect to socio-demographic variables. The prevalence of PPD among mothers will be analysed using PHQ 9.

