### Limitations of the study

The study includes a single group (intervention) and there is no control group to compare the effectiveness of video intervention. The outcome includes only the improvement in knowledge and reduction of stigma on PPD among mothers and does not include assessment of any health-related outcomes such as improved quality of life and prevention of relapse. The mothers are recruited from the immunization clinics at the urban and rural health centres attached to the medical college and not be the actual representation of the community affecting the generalisability of the study findings.

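### The PHQ-9 case rule joins a symptom count to a total score that does not match it, so the same mother can be a case by one and a non-case by the other

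*Protocol article*

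**What the plan says.** The PHQ-9 description under Project implementation plan gives the structure of the tool: "There are nine short statements that make up the scale", and "A mother selects one of the four options that best describes her feelings during the previous two weeks". It then gives the case rule: "Mothers who score 5 or more of the nine depressive symptoms (score >15) are diagnosed with major depression, which requires medical intervention". It does not give the numeric codes of the options or the response level at which a symptom counts as present.

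Three other places rely on a PHQ-9 classification, and none gives a number:

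- Data collection, on referral: "In case a mother scores high on PHQ 9, indicating depression", after which "they will be seen by the trained medical officer".
- Primary outcome, on identifying mothers with postpartum depression: "This will be done using the PHQ 9 before and 4–8 weeks after intervention".
- Statistical analysis: "The prevalence of PPD among mothers will be analysed using PHQ 9".

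Limitations of the study narrows the reach of the PHQ-9: "The outcome includes only the improvement in knowledge and reduction of stigma on PPD among mothers".

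**The concern.** The bracketed score follows the symptom count as though it restated it. A count of items above some level and a sum over all items are different quantities, so a reader who applies one half of the sentence can classify a mother differently from a reader who applies the other.

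Two things depend on the rule: which mothers are sent to the medical officer, and which are counted in the PHQ-9 prevalence at the two screens. Clinical review can correct a mother flagged unnecessarily. It cannot recover one who was never flagged.

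**Working it through.** **Inputs.** Nine items, four options each, a count of at least 5, a total above 15 (all from the PHQ-9 description), and 130 mothers (Sample size). Assumption: options coded 0, 1, 2, 3. The level at which a symptom is present is not stated, so all three possible levels are tried.

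**Step 1: single response patterns.**

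- Five items at 2, four at 0: total = 5×2 + 4×0 = 10. If a symptom counts from level 1 or level 2, the count is 5 (met), but 10 is not above 15.
- Five items at 3, four at 0: total = 5×3 = 15. The count is 5 at every level, but 15 is not above 15. So meeting the count never guarantees meeting the score.
- Four items at 3, five at 1: total = 4×3 + 5×1 = 17, above 15. If a symptom counts from level 2, the count is only 4.

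**Step 2: totals reachable.**

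| Symptom present at | Exactly five symptoms | Exactly four symptoms | Totals shared by ≥5 and ≤4 symptoms |
|---|---|---|---|
| level ≥1 | 5×1 to 5×3 = 5–15 | 4×1 to 4×3 = 4–12 | 5–12 |
| level ≥2 | 5×2 to 5×3+4×1 = 10–19 | 4×2 to 4×3+5×1 = 8–17 | 10–17 |
| level 3 | 5×3 to 5×3+4×2 = 15–23 | 4×3 to 4×3+5×2 = 12–22 | 15–22 |

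Because totals with five or more symptoms overlap totals with four or fewer at every level, no total cut-off, 15 or any other, reproduces the count.

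**Step 3: all patterns.** There are 4^9 = 262,144 response patterns, of which 72,920 total above 15.

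| Symptom present at | Both met | Count only | Score only |
|---|---|---|---|
| level ≥1 | 72,920 | 176,398 | 0 |
| level ≥2 | 71,660 | 59,412 | 1,260 |
| level 3 | 12,700 | 126 | 60,220 |

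**Step 4: both conditions required.** At level ≥1 the joint rule keeps 72,920 of the 72,920 patterns above 15, so the count does nothing. At level ≥2 it keeps 71,660, a loss of 72,920 − 71,660 = 1,260 (1.7%). At level 3 it keeps only 12,700, so there the joint rule is much stricter than the score alone.

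**Step 5: other coding.** With options coded 1 to 4, every total rises by 9. The count-only and score-only patterns become 840 and 9,156 (second option or higher), 0 and 126,562 (third or higher), 0 and 244,808 (fourth). The rules still differ in every case.

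**Step 6: size per mother.** 1/130 = 0.0077, or 0.77 percentage points of prevalence for each mother classified differently.

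Pattern counts treat all response patterns alike. They show that the rules differ; they do not say how many mothers would be affected.

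**The case against.** The best defence is that the sentence never says the two criteria are the same. The bracket can be read as a second requirement: at least five symptoms and a total above 15. That rule is coherent, and at level ≥1 or ≥2 it is the total-score rule or very nearly so. The referral wording in Data collection also speaks of a high score, which points to a total. Option codes and item levels are scoring details of a published instrument that a condensed article may leave out.

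Much of this stands. The text does not assert equivalence, and the missing codes and item levels are not the finding. What remains is that the joint requirement is not stated either, that no other section gives a number to settle the matter, and that under the joint reading the count adds nothing or almost nothing at the two lower item levels.

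A reader might go further and infer any of the following, none of which the document supports:

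- *The study's main result is at risk, since the PHQ-9 appears under Primary outcome.* Limitations of the study confines the outcome to knowledge and stigma, Primary outcome ties awareness and stigma to the PoDLiS, and the PHQ-9 gets one descriptive sentence in Statistical analysis.
- *Many mothers will be missed.* No PHQ-9 distribution is given, so no number can be put on it.
- *The before-and-after prevalence is biased.* Inconsistent use of the two criteria could shift it by definition alone, but nothing shows that different rules would be applied at the two screens.
- *A cut-off above 15 is wrong.* The document gives no basis for preferring another value.

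**Conclusion.** The concern holds in a limited form. The PHQ-9 sentence combines two criteria that are not equivalent at any item level, under 0–3 or 1–4 coding, so it does not fix who is a case. The clearest example, a mother totalling 10 with five items at level 2, rests on 0–3 coding and on a symptom counting from level 1 or 2.

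This is a contradictory threshold rather than an omitted detail, because the article states a rule and the rule can give two answers. Its reach is referral and the descriptive PHQ-9 prevalence only; its size in mothers cannot be estimated from the document. The sample size, which rests on awareness, and the PoDLiS analysis do not use the rule.

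**What to change.** Before data collection, delete the symptom count from the PHQ-9 sentence and keep one stated total-score cut-off, with the option coding given beside it. This matches the referral wording in Data collection. The document's own number is a total above 15; it should stand unless the sponsor confirms another. Put the same number in place of the unquantified high score in Data collection, apply it for referral at both the pre-test and the post-test screen, and use it as the numerator of the prevalence in Statistical analysis.

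The cost is one sentence in the protocol and one line in the site procedure, with no extra data. The downside is that any single cut-off trades missed mothers against extra referrals: a lower one sends more women to the medical officer, a higher one misses more.

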### Procedure

**Development of Video Intervention**

The steps involved in video development will be as follows:

**(i) Development of script**
a) Literature review: The script for the video will be based on a thorough literature search using PubMed, Psycinfo, Elsevier, Google scholar. The key words for the literature search will be Postpartum Depression, experiences, risk factors, identification, stigma, social support and management. Articles published over the past 10 years in peer reviewed indexed publications in the English language or providing an abstract (with complete information) will be included. Also the articles and blogs published in English/Kannada/Hindi on the website of the Perinatal Psychiatry services in India focussing on factors associated with Postpartum Depression will be considered. All the articles and blogs considered will be screened for authenticity of information by the perinatal psychiatry experts in the team.
b) Focus Group Discussion (FGD): Separate FGD’s among the mother’s and the healthcare experts will be conducted. The minimum of 5 to maximum 10 members will be considered for the FGD’s. The FGD’s are planned to be conducted in 2 rounds or until the intended saturation level has been achieved. The mothers within 18 months of child birth will be considered. The healthcare experts include both doctors and non-doctors working in the field of Perinatal mental health such as Psychiatry, Psychiatric Social Work, Clinical Psychology, Nursing, Obstetrics, Pediatrics, Public Health, Yoga etc. The FGD among mothers will be conducted in the immunization clinics at urban and rural Primary health centers. The FGD among health care experts will be conducted online using video conference platform for the ensuring participation of multidisciplinary team located in different geographical distribution. Separate FGD guides will be developed covering topics on prevalence, risk factors, presentation, barriers and support, and role of educational interventions in prevention and management of PPD. The same will also be qualitatively analyzed.**(ii) Finalising the script**
The final script will be in the form of a story line about the experience of a mother with PPD covering the aspects of the symptoms, stigma associated, barriers for help seeking and management. The script will be finalised based on the literature review and the findings from focus group discussions with mothers and the experts, so that the relevant cultural context is being considered. The developed script will be finalised in discussion with the experts in the internal project team.**(iii) Writing the ‘shooting script’**
The finalized script will be transformed into a shooting script of around 10–12 pages with inputs from the video Production team to get a final video of 12–15 minutes’ duration. The shooting script will include aspects of filming such as camera angles and cut or fade instructions from one actor to another or to experts.**(iv) Video production**
The characters for the videos as well as the locations for the shoots will be identified. Written informed consent will be obtained from the experts and actors. The video will be made as such that it is relatable for those receiving the intervention. The characters chosen for the study will be sensitive and act in a manner that does not hurt the feelings of anyone. The videos will be recorded and edited as per the requirement.**(v) Finalising the video**
The video will be finalised by the internal team of experts and later will be screened among experts working in perinatal mental health and mothers and the valid suggestions will be incorporated.

### Data collection

The Postpartum Depression literacy scale will be used to conduct the pre and post-test among the postpartum mothers to examine the effectiveness of the video intervention in terms of improving awareness and reducing the stigma. The literacy scale is a self-report measure which will be easy to administer, however in case of mothers who are illiterate, the scale will be administered by the research scholar. The postpartum mothers visiting the Immunization Clinic will undertake the pre-test, screened for PPD and later will be made to watch the video. After watching the video, a feedback form will be provided to the mothers regarding the effectiveness of the video. The post-test will be conducted at an interval of 4–8 weeks of time after pre-test [35] to ensure knowledge retention and also the compliance for posttest, as the mothers will be visiting immunization clinics at 6, 10 and 14 weeks for vaccination of the child as part of the Universal Immunization Program [36]. Lastly the mothers will be re-screened for PPD using PHQ 9. In case a mother scores high on PHQ 9, indicating depression them they will be seen by the trained medical officer (As a part of District Mental Health Program (DMHP), all the PHCs runs ‘Manochaitanya Clinic’ on Tuesdays.) and later mothers will be referred to manochiatanya clinic for further evaluation and treatment by mental health professionals.

### Study outcome

#### Primary outcome

This video intervention is intended to improve the awareness and reduce stigma on postpartum depression among mothers attending immunization clinics. The same will be assessed using the PoDLiS scale before and after the intervention.The developed educational video will be useful to help identify mothers with PPD which can then lead to early initiation of treatment and improved health outcomes for both mothers and their children. This will be done using the PHQ 9 before and 4–8 weeks after intervention.

#### Secondary outcome

The developed video intervention can be utilised in future as an educational tool to improve perinatal mental health literacy and reduce stigma among expectant mothers, postpartum mothers, family members and community.The video can also be used for capacity building and training of health professionals and healthcare workers working in the area of perinatal mental health.

#### Data management plan

The collected data will be kept anonymous using unique IDs, data will be entered in a dedicated laptop which will be password protected and only the research team will be provided the access.

### Statistical analysis

The salient findings from literature search will be summarized and findings will be included for the script. The outcomes of FGDs will be qualitatively analysed. Inductive and thematic theme identification will be done using a descriptive approach. The analysis will be done manually and the themes will be generated based on the codes from the discussion. The findings will be utilized for finalising the video script. The effectiveness of the video intervention will be quantitatively analysed using paired t test. The results will be presented as mean, SD at each time point and 95% CI of the difference between pre and post means. Repeated measures of ANOVA will be used to analyse the change in Postpartum Depression Literacy Scale scores with respect to socio-demographic variables. The prevalence of PPD among mothers will be analysed using PHQ 9.

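### The PHQ-9 is used as a screen with referral for further evaluation, yet its positive share is to be reported as the prevalence of PPD

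*Protocol article*

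**What the plan says.** The protocol article gives the PHQ-9 result different standing in different places.

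- **Screen.** The Abstract (Materials and methods) describes screening for PPD with the PHQ-9. The PHQ 9 entry under Project implementation plan states: "The PHQ 9 tool will be administered to screen the mothers for depression in the study". Data collection has mothers screened at the start and screened again at the post-test.
- **Screen followed by evaluation.** Data collection opens the referral pathway with "In case a mother scores high on PHQ 9, indicating depression". A trained medical officer sees such a mother, and she is then "referred to manochiatanya clinic for further evaluation and treatment by mental health professionals".
- **Diagnosis.** The same PHQ 9 entry states: "Mothers who score 5 or more of the nine depressive symptoms (score >15) are diagnosed with major depression, which requires medical intervention". It also describes the instrument as a "quick self-report tool that is frequently used for screening and diagnosis".
- **Case count.** Statistical analysis states: "The prevalence of PPD among mothers will be analysed using PHQ 9".

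The Primary outcome section lists PHQ-9 identification of mothers with PPD, before and 4–8 weeks after the intervention, beside the PoDLiS. The prevalence sentence is the only analysis that names the PHQ-9.

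**The concern.** If a positive PHQ-9 still needs evaluation by mental health professionals, the mother's status is open when the questionnaire is scored. A prevalence taken from the PHQ-9 alone treats that status as settled. The PHQ-9 is the only PPD measure named, and no section says that the clinic's findings are collected or used to count cases. The published figure would therefore be a screen-positive proportion carrying the name of a disease prevalence.

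Setting a cut-off later would not cure this, because every cut-off yields a screen-positive share. At stake is what the trial may say about how common PPD was among these mothers. The estimate of the video's effect on literacy is not at stake.

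**Working it through.** **The plan's own figures.** The document computes nothing for the PHQ-9. Its one computed figure, a sample size of 128, reproduces: a paired t test with effect size 0.25, two-sided 5% and 80% power needs 128 (power 0.8015). It is not in dispute and does not bear on this point.

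**The text.** Suppose the PHQ 9 entry has already diagnosed the mother. Then the evaluation in Data collection does not decide her status. Suppose instead that the evaluation does decide it. Then the prevalence sentence counts mothers whose status is undecided. The text does not say which holds.

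**How far a screen-positive share can lie from prevalence.** Inputs:

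- n = 130 (Sample size section).
- True prevalence p = 22%, the figure for India in the Introduction, used only as an illustration. Also p = 10%, which is an assumption. A lower value is worth showing because the exclusion criteria remove mothers with a diagnosed mental health condition.
- Sensitivity (Se) and specificity (Sp): the documents give none, so all values are assumed.

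Formulas:

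- Reported share = p × Se + (1 − p) × (1 − Sp).
- False share of counted cases = (1 − p)(1 − Sp) / reported share.
- SE = √(p(1 − p)/130). This is √(0.22 × 0.78/130) = 0.0363 at 22%, and √(0.10 × 0.90/130) = 0.0263 at 10%.

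| p | Se / Sp | Reported share | Error in SE | False share |
|---|---|---|---|---|
| 22% | 0.50 / 0.97 | 0.110 + 0.0234 = 13.3% | −0.0866/0.0363 = −2.4 | 18% |
| 22% | 0.80 / 0.90 | 0.176 + 0.078 = 25.4% | 0.034/0.0363 = +0.9 | 31% |
| 22% | 0.85 / 0.85 | 0.187 + 0.117 = 30.4% | 0.084/0.0363 = +2.3 | 38% |
| 10% | 0.80 / 0.90 | 0.080 + 0.090 = 17.0% | 0.070/0.0263 = +2.7 | 53% |

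These are four chosen scenarios and not limits. Over a grid with Se 0.70–0.90 and Sp 0.80–0.95, the reported share runs from 19.3% to 35.4% at a true 22%, and from 11.5% to 27.0% at a true 10%. The upper ends are (0.354 − 0.22)/0.0363 = 3.7 SE and (0.270 − 0.10)/0.0263 = 6.5 SE too high. The sign depends on whether missed cases, p(1 − Se), outnumber false positives, (1 − p)(1 − Sp). The documents do not let a reader tell which.

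**The case against.** The best defence is that the protocol knowingly gives the PHQ-9 both roles, since it says the tool serves for screening and for diagnosis. The prevalence sentence also names its instrument, so no reader is misled about the source. On this view only a preference in wording remains, one that could be raised against any questionnaire survey. The dual-role sentence does explain the mixed language. It does not reconcile a diagnosis made by score with a pathway in which professionals still have to evaluate the mother. Naming the instrument helps, but the quantity is still called the prevalence of PPD.

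Other parts of the defence stand, and they rule out stronger readings that a reader might infer:

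- *That the sections contain rival case definitions.* Data collection describes a referral pathway and defines no PPD case.
- *That a planned confidence interval would be too narrow.* No interval is planned for the prevalence. The 95% CI in Statistical analysis is for the difference between pre and post means.
- *That prevalence will be overstated, or will be compared unfairly with 22%.* The direction is unknown. The article also does not say how the 22% was measured.
- *That a primary result is compromised.* The PHQ-9 does appear under Primary outcome. However, the Objectives, the awareness-based sample size and the Limitations section all make knowledge and stigma the outcome of effectiveness.
- *That a missing cut-off is the fault.* An article may leave that to the full plan.

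**Conclusion.** The point holds as a matter of labelling and consistency. Followed as written, the plan reports an unconfirmed PHQ-9-positive share as PPD prevalence, while elsewhere it treats a high score as a reason for further evaluation. This conclusion rests on the text alone.

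The numerical size rests wholly on assumed sensitivity, specificity and true prevalence. The four scenarios span 2.4 SE too low to 2.7 SE too high, and other plausible pairs go further. They show that the gap can exceed sampling error in either direction. They do not estimate the error in this trial; in one middle scenario it is only 0.9 SE. The prevalence is a descriptive result of secondary weight, and the PoDLiS comparison does not depend on it.

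**What to change.** In Statistical analysis, label the estimate as the proportion screening positive on the PHQ-9, with 95% CI, at each time point (start of trial and post-test at 4–8 weeks). Do not present it as PPD prevalence. If the results of the referral evaluation are available, report the number confirmed among those referred on a separate line.

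The sponsor must also reconcile the diagnosis wording in the PHQ 9 entry with the further evaluation in Data collection. That sentence also says when medical intervention is required, so no replacement wording, threshold or clinical rule is proposed here.

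The cost is a change of wording and table labels, with no new visits or staff. The downside is that the trial can no longer state a PPD prevalence from the PHQ-9 alone.
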